## Outcome measures

### Primary

The International Hip Outcome Tool–12 (iHOT-12) PROM scores at baseline, 3, 6 and 12 months will be compared within and between the PRP and normal saline arms.

### Secondary

The visual analogue score (VAS) for pain, the Modified Harris Hip Score (mHHS) and the three-level version of the EuroQol five-dimensional (EQ-5D 3 L) questionnaire PROM scores will be collected at baseline, 3, 6 and 12 months and will be compared within and between the PRP and normal saline arms (Fig. 1).

**Fig. 1 Fig1:**
[figure not shown]
Standard protocol items: recommendation for interventional trials (SPIRIT) flow diagram. A summary of the planned study interventions and assessments. MRI, magnetic resonance imaging; iHOT-12, International Hip Outcome Tool-12; VAS, visual analogue score; EQ-5D 3 L, Three-level version of the EuroQol five-dimensional questionnaire; MHHS, Modified Harris Hip Score; PRP, platelet-rich plasma

### End of the trial

Recruitment will cease once the last participant has been recruited following our sample size recommendations. The trial will cease once the last patient has attended their 12 months follow up (Fig. 2).

**Fig. 2 Fig2:**
[figure not shown]
Study flow chart. GTPS, greater trochanteric pain syndrome; R&D, Research and Development; PROM, patient-reported outcome measure; PRP, platelet-rich plasma; physio, physiotherapy

## Data management

The data collected from the trial will be entered into a trial database. The database will be agreed and set up by our information technology (IT) technician, statistician and PI. The database will be stored securely on our computer systems in the hospital. During the interim analysis, the database will be frozen to ensure data collected after this point are not included in the interim report. Access to the data will be limited to those only directly involved in the trial and who are part of the research team. The data will be anonymised in terms of participant identifiable data and will only contain demographic details. Identifiable participant data will be held on a separate database in our secure computer network in the hospital. Each participant will have a unique participant code so their outcome data can be matched with their personal identifiable data if required. All physical data will be stored in the Research and Development Office, North Tyneside General Hospital in a locked cabinet. The office is secured by a code-operated lock and is only accessible by the research team. All computer data will be stored on our secure password-protected National Health Service (NHS) Trust computers. Data will be archived in accordance with the Research and Development Department, Northumbria Healthcare NHS Foundation Trust guidance. A data monitoring committee will be formed and will convene for this trial.

### Data Monitoring Committee

A Data Monitoring Committee will convene at the interim period of 50% recruitment at 6-month follow up. This will be chaired by the PI and include other co-investigators, a trial coordinator and ideally a member of our patient focus group. All issues relating to the management and conduct of the trial will be reviewed and addressed. Meeting times will be an interim meeting at 50% recruitment reaching 6-month follow up and the end of trial.

### Statistical analysis

#### Statistician report

The primary outcome of interest is the change from baseline to 12-month follow up in the iHOT-12, comparing the PRP and placebo group. The study will be run as a superiority trial. The cut-off for statistical significance is set at 5% and desired power at 90%, with two-tailed tests applied. Data on change from baseline are also assumed to be parametric and the *t* test will be applied to the data to assess statistical significance.

The minimally clinically important difference (MCID) for the iHOT-12 has been reported by Sansone et al. as 10 (from 100) and the standard deviation for the change in score from baseline as no greater than 21 [25]. Although, there are few previous data on which to base a sample size calculation, Monto et al. compared change from baseline to 12-month follow up in a group of 40 patient with hip bursitis, with steroids and PRP as the interventions being compared. In the PRP group Harris Hip scores increased from 51.7 to 87.4 whilst in the steroid group, scores increased from 50.5 to 58.8 at 12 months [22]. Since the Harris Hip score is also scored from 100, our sample size calculation is based on these figures. We conservatively assume that change in iHOT score from baseline in the placebo group will be no more than in the steroid group reported by Monto et al., and estimate a maximal change of 10. We also estimate that the change in the iHOT score from baseline in the PRP group will be no less than 27. Using these figures, a minimal sample size at follow up of 66 (33 in each group) will be required.

Pilot data obtained by our team suggest that the rate of refusal to participate should be no more than 25% and the dropout rate no more than 35% over 12 months. Refusal rates tend to be low in this patient group given the chronic nature of the condition and the fact that patients will only be approached once conservative management has failed. Thus, we will need to approach 135.4 (rounded up to 136) patients, and recruit 102 patients to achieve our target sample size.

Data will be analysed using standard statistical software (e.g. SPSS and SAS). In the first instance, data will be analysed using simple descriptive statistics to compare the two groups in terms of demographics, clinical characteristics at baseline and outcomes. The primary outcome of interest will be the change from baseline to 12-month follow up in the iHOT-12, comparing the PRP and placebo group. The iHOT-12 data are expected to be parametric and so the unpaired *t* test will be used to compare the difference in change from baseline in the two groups. Since randomisation will not be stratified, we will also look to adjust for the possible confounding influence of differences in baseline characteristics (e.g. age, gender and body mass index (BMI)) using multivariable methods (e.g. linear regression). The significance level for all inferential tests will be set at 5%.

In secondary analysis, we will investigate changes in visual analogue pain score, EQ-5D 3 L and modified Harris Hip score in the two groups, as for the primary outcome. In sub-group analysis, we will investigate the data based on specific previous treatment, patients who required more than one treatment and patients with the highest levels of baseline pain.

The test group (PRP) alone: for all outcome measures the difference between the follow up scores with baseline will be assessed (e.g. baseline versus 3 months, baseline versus 12 months). The difference between one follow up period to the next will be examined (e.g. 3 months versus 6 months, 6 months versus 12 months). A significant difference will be set at a *p* value of less than 0.05.

The placebo group (normal saline) alone: data will be analysed as for the test group, as described.

Test versus placebo: for all outcome measures, the differential change at each follow up time point will be compared between the trial arms and the significance value calculated.

Statistical tests will be performed to ensure that gender, BMI and age differences are not significantly associated with a particular result. Care will be taken to minimise missing responses and to continue to follow up those who withdraw from treatment.

We will only be using the completed cases for final analyses; the remainder will be excluded.

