**Methods/design:**

HIPPO is a single-centre, double-blind randomized placebo-controlled study in patients with a radiologically confirmed diagnosis of gluteus medius or minimus tendinopathy with swelling within the tendon insertion with or without bursitis. We aim to randomise 102 patients with GTPS to either the PRP or placebo (normal saline injection) treatment arm. Participants will receive one ultrasound (US) guided PRP/placebo injection into the trochanteric bursa and surrounding gluteus medius/minimus tendons. The primary outcome measure is the International Hip Outcome Tool-12. Secondary outcome measures will include a visual analogue score for pain, the three-level version of the EuroQol five-dimensional questionnaire and the modified Harris Hip Score. Outcomes will be measured at baseline, 3, 6 and 12 months. Participants will have the option at 6 months to have a repeat blinded injection or cross over to PRP. Analyses of primary and secondary outcomes will be made according to the intention-to-treat principle. The trial reporting will comply with Consolidated Standards of Reporting Trials (CONSORT) guidelines.

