## Methods

### Trial design

The trial will be a two-arm, single-centre, double-blind, randomised control trial (RCT). The study will include a two-way comparison between PRP and placebo normal saline injections for treating GTPS. The trial design has been based on our local experience with using PRP in patients with GTPS and an RCT conducted by Monto et al. in 2014 [22] comparing steroid injection with PRP in patients with severe hip bursitis. Add to this, a pilot study by Ribeiro et al. in 2016 [23], which compared the efficacy of PRP against corticosteroid in the treatment of GTPS.

Participants will be identified and referred for inclusion in the study by their main care provider (general practitioner (GP), orthopaedic surgeon, rheumatologist or extended-scope physiotherapy practitioner). They will then be invited for a first interview where eligibility will be assessed, further information about the study will be given and written consent for inclusion obtained. Potential participants will be permitted to reschedule another interview appointment if they need more time to think about whether they wish to participate. Participants will be allocated randomly to either the PRP or normal saline injection treatment arm. They will receive their treatment under sterile conditions under ultrasound guidance by a consultant rheumatologist (IA). The participant will be contacted by phone a week after receiving treatment to monitor for early adverse events. Participants and outcome assessors will be blinded to treatment arm. Participants will be reviewed at baseline, 3, 6 and 12 months with patient-reported outcome measures (PROM) completed at each of these reviews. During the 6 months follow up participants will be given the option of a repeat injection of their original treatment or if they specifically request PRP then we will offer this to them but maintain the blinding of their original treatment. This was a key ethical discussion point in our focus group meeting engaging patient and public involvement in that expecting participants to potentially continue with placebo for a further 6 months while in pain would place a significant burden on them. The trial is expected to last approximately 4 years allowing 18–24 months for recruitment with the remaining time used to complete the follow up period until the last patient recruited.

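### The 12-month primary comparison is diluted and partly unblinded by optional PRP from 6 months, and the sample size makes no allowance for it

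*Protocol article*

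**What the plan says.** The Statistician report names one time point for the primary comparison: "The primary outcome of interest is the change from baseline to 12-month follow up in the iHOT-12, comparing the PRP and placebo group". The test is an unpaired t test on change from baseline. The Primary outcome section is looser and lists iHOT-12 at baseline, 3, 6 and 12 months, within and between arms.

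The abstract describes what happens half-way: "Participants will have the option at 6 months to have a repeat blinded injection or cross over to PRP". Under Trial design, participants may repeat their original treatment, or "if they specifically request PRP then we will offer this to them but maintain the blinding of their original treatment". The reason given is that "expecting participants to potentially continue with placebo for a further 6 months while in pain would place a significant burden on them".

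On the analysis set, the abstract states "Analyses of primary and secondary outcomes will be made according to the intention-to-treat principle", while the Statistical analysis section ends with "We will only be using the completed cases for final analyses; the remainder will be excluded". That section also plans a between-arm comparison at each follow-up for all outcomes. Its only mention of re-treated participants is a subgroup analysis that includes "patients who required more than one treatment and patients with the highest levels of baseline pain".

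**The concern.** The Aims ask whether PRP works better than a saline injection. At 12 months the arms no longer represent those two treatments. The placebo arm may contain people given saline only and people given saline then PRP. The PRP arm may contain people with one PRP injection and people with two.

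Blinding is also affected. Someone who asks for PRP and gets it does not learn the original allocation, but does know what was injected at 6 months. The iHOT-12 is completed by the patient, so that knowledge can influence the 12-month score.

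Uptake is unlikely to be random. The option was created for people still in pain, so placebo participants with poor results are the likeliest to use it. If PRP works, their later improvement is credited to the placebo arm. A null 12-month result could then mean that PRP does not work, or that enough placebo participants received it. Duration of effect after one injection, the other stated aim, is equally hard to read from arms that contain re-injected people.

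**Working it through.** **Inputs, all from the Statistician report.** Assumed change is 27 points (PRP) and 10 points (placebo), so the difference is 17. The SD of change is 21. For the error rates: "The cut-off for statistical significance is set at 5% and desired power at 90%, with two-tailed tests applied". Evaluable sample is 66 (33 per arm), dropout 35%, recruitment target 102. The MCID is 10 points.

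**Reproducing the plan's figure.** Normal approximation: n per arm = 2 × (1.960 + 1.282)² × 21² / 17² = 32.07, rounded up to 33. Recruitment: 66 / (1 − 0.35) = 101.5, rounded up to 102. At 33 per arm the standard error of the difference is 21 × √(2/33) = 5.17. With the noncentral t on 64 degrees of freedom, power is 89.9%. The stated sample size is thus fully explained by the difference, the SD and the dropout rate, and nothing is left over for crossover.

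**Adding crossover.** Let c be the fraction of the placebo arm that receives PRP at 6 months, and f the share of the 17-point benefit that they have gained by month 12. The expected difference by original arm is 17 × (1 − c × f). The article gives neither c nor f, so both are assumptions. SD is held at 21 and the arms at 33.

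| Placebo arm crossing over (c) | Difference, full benefit (f = 1) | Power | Difference, half benefit (f = 0.5) | Power |
|---|---|---|---|---|
| 0% | 17.0 | 90% | 17.0 | 90% |
| 20% | 13.6 | 74% | 15.3 | 83% |
| 30% | 11.9 | 62% | 14.45 | 79% |
| 50% | 8.5 | 37% | 12.75 | 68% |

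With full benefit, the expected difference falls to the 10-point MCID at c = 1 − 10/17 = 41%, where power is 48%. Restoring 90% power at 20% crossover with full benefit needs 52 evaluable per arm, so 104 / 0.65 = 160 recruits against 102 planned.

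**What the table leaves out.** It changes the placebo arm only. If second PRP injections raise the PRP-arm mean by g points, the difference becomes 17 × (1 − c × f) + g. The article gives no basis for g.

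**At 6 months.** If questionnaires are completed before a second injection is offered, c = 0. The stated 66 evaluable and 102 recruited then stand, provided that the 17-point difference and SD of 21 also hold at 6 months.

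**The case against.** The strongest reply is that the plan loses less than it seems to.

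- **A reader might infer that the randomised, blinded contrast is gone by 12 months.** The documents do not support that. Comparison by randomised arm survives and answers a legitimate treatment-policy question. Original allocation stays masked, the abstract calls the repeat injection blinded, and only those who ask for PRP know what they received.
- **The plan is not silent on the problem.** It includes a between-arm test at 6 months and a subgroup of re-treated patients, so a null 12-month result would be read beside a 6-month one. This stands, but the 6-month test is not primary, and a subgroup formed by events after randomisation cannot recover the randomised comparison.
- **The direction of bias is not certain.** Repeat PRP in the PRP arm, possibly known to the patient, could widen the difference. Dilution is the likelier result if PRP works, but the net effect depends on uptake in both arms.
- **The full-benefit figures are near the worst case.** They assume that people who did poorly catch up completely. The plan also used 17 points where its cited steroid comparison gives (87.4 − 51.7) − (58.8 − 50.5) = 27.4; on that figure, crossover of 1 − 17/27.4 = 38% would still leave 17. The plan does not present this margin as a crossover allowance, however, and the source used another score and a steroid comparator.
- **Moving the primary time point has risks.** Recruitment has started, and the interim meeting, chaired by the principal investigator, is tied to 6-month follow-up. A change made after a look at those data by arm could appear data-driven. This stands and governs the timing of the fix.

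**Conclusion.** The point holds as a design flaw in the primary comparison. At 12 months the planned test compares PRP, once or twice, with saline plus optional PRP from month 6, some of it knowingly received. That is not the comparison in the Aims, and the 90% power applies only without crossover.

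The size cannot be fixed from the article. For assumed placebo-arm crossover of 20% to 50%, power runs from 74% down to 37% with full benefit in crossers, and from 83% down to 68% with half benefit. These figures rest on the plan's 17-point difference, SD of 21, 33 evaluable per arm and no gain from second PRP injections. With low uptake the damage is modest. None of them should be quoted as the trial's actual power.

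A reader might also infer that the completed-cases rule removes crossers. The text does not say so. It does conflict with the intention-to-treat statement, so the handling of re-injected participants must be stated whichever time point is primary.

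**What to change.** 1. Make the between-arm difference in iHOT-12 change from baseline to 6 months the primary contrast, and state that the 6-month questionnaires are completed before a second injection is offered.
2. Settle this, and update the registration, before any interim look at 6-month data by arm. Record that the decision was made without such data.
3. Keep 12 months as the key secondary comparison, labelled *PRP versus placebo with optional PRP from 6 months*.
4. Add a 12-month estimate that sets aside scores recorded after a second injection, from a mixed model on the 3-, 6- and 12-month data. This assumes that, given earlier scores, re-injected participants would have followed a course like that of similar participants who were not re-injected. That assumption should be stated.
5. If 12 months stays primary, say that it estimates the treatment policy in item 3, add the estimate in item 4, and restate the 90% power as holding only with no crossover.

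The crossover option is untouched, and no visits or patients are added. The cost is protocol and analysis-plan wording and a registry update. There are two real downsides. The headline claim becomes a 6-month claim although the planning figures come from a 12-month source, and duration of effect, a stated aim, then rests on secondary analyses.

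### The primary test compares iHOT-12 change without adjusting for baseline iHOT-12: valid, but usually less precise than a baseline-adjusted model that needs no new data

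*Protocol article*

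**What the plan says.** The Statistician report (protocol article, Statistical analysis) defines the endpoint: "The primary outcome of interest will be the change from baseline to 12-month follow up in the iHOT-12, comparing the PRP and placebo group". It then fixes the test: "the unpaired *t* test will be used to compare the difference in change from baseline in the two groups". That test carries no covariate.

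A further analysis is announced, for which the reason given is "Since randomisation will not be stratified". Its purpose is worded as "adjust for the possible confounding influence of differences in baseline characteristics (e.g. age, gender and body mass index (BMI". Regression is mentioned as one possible technique, so both the covariates and the method are given as examples.

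Later in the same section: "Statistical tests will be performed to ensure that gender, BMI and age differences are not significantly associated with a particular result".

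Baseline iHOT-12 is available. Under Outcome measures, Primary, the iHOT-12 "PROM scores at baseline, 3, 6 and 12 months will be compared within and between the PRP and normal saline arms", and the Consent section has baseline questionnaires recorded once the participant has consented. Nothing in the section names the baseline score as a covariate. The secondary outcomes (VAS, EQ-5D, mHHS) are to be analysed in the same way as the primary.

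**The concern.** A change score amounts to a baseline-adjusted analysis in which the slope of follow-up on baseline is forced to equal 1. If the true slope is below 1, subtracting the whole baseline over-corrects. This adds noise and shifts the estimate in favour of whichever arm happened to start worse. Estimating the slope removes both problems.

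Randomisation is unstratified, so nothing in the described design balances baseline iHOT-12. About 66 completers are expected, and the sample size rests on a 17-point difference, while the MCID quoted in the same section is 10. Precision therefore matters if the true effect is smaller than planned.

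The sentence on gender, BMI and age is a related weakness. A non-significant association in about 66 people cannot show that a covariate has no influence. Covariates are better chosen beforehand for their expected prognostic value.

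**Working it through.** **Inputs from the Statistician report.** Change of 10 on placebo and 27 on PRP (difference 17); SD of change 21; two-sided 5%; 90% power; 33 per arm at follow-up; 35% dropout; MCID 10.

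**Assumed, because the article does not give them.** r, the within-arm correlation of baseline with 12-month iHOT-12: 0.3, 0.5, 0.7. k, the follow-up SD divided by the baseline SD: 1, 1.25, 1.5. The SD of change is held at 21 throughout.

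**Step 1: reproduce the plan.** n per arm = 2 × [21 × (1.960 + 1.282) / 17]² = 32.07, rounded up to 33, so 66 in total. Then 66 / 0.65 = 101.5, rounded up to 102, and 101.5 / 0.75 = 135.4, rounded up to 136. All match. The exact noncentral t gives 89.9% power at 33 per arm (34 per arm would pass 90%), which is a trivial difference. The SE of the difference is 21 × √(2/33) = 5.17 points. Power at 10 points is 47.8%.

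**Step 2: variance ratio.** With baseline SD s:
- Var(change) = s²(1 + k² − 2rk)
- ANCOVA residual variance = k²s²(1 − r²)
- Ratio = k²(1 − r²) / (1 + k² − 2rk), which reduces to (1 + r)/2 when k = 1
- Slope of follow-up on baseline = rk

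**Step 3: results at 33 per arm.** ANCOVA SD = 21 × √ratio; SE = SD × √(2/33); power by noncentral t on 63 degrees of freedom.

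| k | r | Slope | Ratio | Variance cut | SE | Power, 17 points | Power, 10 points |
|---|---|---|---|---|---|---|---|
| t test on change | – | (1) | 1 | – | 5.17 | 89.9% | 47.8% |
| 1 | 0.3 | 0.30 | 0.650 | 35% | 4.17 | 98.0% | 65.6% |
| 1 | 0.5 | 0.50 | 0.750 | 25% | 4.48 | 96.2% | 59.5% |
| 1 | 0.7 | 0.70 | 0.850 | 15% | 4.77 | 94.0% | 54.2% |
| 1.25 | 0.3 | 0.375 | 0.784 | 22% | 4.58 | 95.5% | 57.6% |
| 1.25 | 0.5 | 0.625 | 0.893 | 11% | 4.89 | 92.9% | 52.2% |
| 1.25 | 0.7 | 0.875 | 0.981 | 2% | 5.12 | 90.5% | 48.6% |
| 1.5 | 0.3 | 0.45 | 0.871 | 13% | 4.83 | 93.4% | 53.2% |
| 1.5 | 0.5 | 0.75 | 0.964 | 4% | 5.08 | 90.9% | 49.2% |
| 1.5 | 0.7 | 1.05 | 0.998 | about 0% | 5.16 | 90.0% | 47.9% |

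**Step 4: chance imbalance.** Given an observed baseline difference, the change-score estimate is shifted by (slope − 1) × difference. With k = 1, a 5-point imbalance shifts it by 3.5, 2.5 or 1.5 points at r = 0.3, 0.5 or 0.7, favouring the arm with the worse baseline. For an imbalance of one SE, the baseline SD is 21 / √(2(1 − r)) = 17.7, 21.0 or 27.1, so one SE is 4.4, 5.2 or 6.7 points and the shift is 3.1, 2.6 or 2.0 points. At k = 1.5 and r = 0.7 the slope exceeds 1 and the direction reverses.

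**Step 5: validity.** In 20,000 simulated trials with no effect (33 per arm, r = 0.5, equal SDs), the t test on change rejected in 5.0%, and the mean estimate was 0.03 points.

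**The case against.** The best defence is that nothing here is an error in the result. The endpoint, the SD of change and the power calculation all fit the t test on change. The test is unbiased over randomisation and keeps its 5% error rate, and the sample size reproduces. This stands in full, so the point is about efficiency.

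It is also fair that the size of the gain is unknown. If the 12-month scores are more spread out than the baseline scores, the gain shrinks, and it nearly vanishes once the slope is close to 1. That stands too, so the full range belongs with the claim.

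A reader might infer four stronger charges that the text does not support:
- *Baseline iHOT-12 is excluded.* The covariates are given as examples, so it is unnamed rather than ruled out, and an analysis plan that is not shown could name it in the supplementary model. The stated primary test would still be unadjusted.
- *Two analyses compete with no rule for which decides.* The t test is attached to the primary outcome, and the adjustment is introduced as additional.
- *Adjustment is triggered by observed imbalance or by the covariate tests.* The stated reason is unstratified randomisation, which is known in advance. Nothing says that the later tests select the model.
- *Regression to the mean biases the comparison.* In a randomised comparison it acts on both arms alike in expectation. Only a chance imbalance is carried into a particular estimate, and that variation is already in the t test's SE.

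**Conclusion.** The point holds as an efficiency recommendation. The primary t test is valid and has about 90% power on the plan's own assumptions, but it does not use a baseline score that the trial already collects. In large samples a baseline-adjusted model is at least as precise whatever r and k are, and strictly more precise unless the slope is 1.

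Over the assumed range the variance reduction runs from 35% (r = 0.3, equal SDs) to about nil (r = 0.7, follow-up SD 1.5 times baseline). The practical value is greatest if the true effect is nearer the 10-point MCID than the planned 17: power there is 48% unadjusted and 54% to 66% adjusted with equal SDs, though only 48% to 53% at an SD ratio of 1.5. These figures assume a linear relation with the same slope in both arms and 33 completers per arm. They credit baseline iHOT-12 alone, not age, gender or BMI.

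The sentence promising that significance tests will rule out the influence of gender, BMI and age claims more than such tests can deliver, and it should go.

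**What to change.** Before unblinding, amend the Statistician report as follows:

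1. Make the primary analysis a linear model (ANCOVA) of 12-month iHOT-12 on arm, with baseline iHOT-12 as a pre-specified covariate. Using change as the response in the same model gives the identical treatment estimate.
2. Replace the examples with a closed list of any further covariates (age, gender, BMI), fixed in advance and kept whatever the observed balance.
3. Use the same form, with the matching baseline score, for VAS, mHHS and EQ-5D.
4. Keep the unadjusted t test on change as a supporting analysis.
5. Delete the sentence that relies on significance tests of gender, BMI and age.

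The cost is one paragraph of text and about one degree of freedom per covariate. No new data are needed, and the sample size of 66 completers and 102 recruited need not change for this reason.

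### The planned subgroup of patients needing more than one treatment is, on its natural reading, fixed after randomisation, so a PRP-versus-placebo comparison within it is not protected

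*Protocol article*

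**What the plan says.** The Protocol article, under Statistician report, names three subgroup factors: specific previous treatment, and then "patients who required more than one treatment and patients with the highest levels of baseline pain". It does not mark any of them as descriptive, within-arm or non-randomised. The same section plans that "for all outcome measures, the differential change at each follow up time point will be compared between the trial arms".

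Under Trial design, each participant has one allocated injection, followed by a choice: "During the 6 months follow up participants will be given the option of a repeat injection of their original treatment". The alternative is PRP: "if they specifically request PRP then we will offer this to them but maintain the blinding of their original treatment". The reason given is that "expecting participants to potentially continue with placebo for a further 6 months while in pain would place a significant burden on them". No response threshold is set for taking up the option. The primary outcome is the change in iHOT-12 from baseline to 12 months, which is measured after this choice.

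**The concern.** The other two subgroup factors can be known at baseline. This one, if it means the second injection, is known only about 6 months after allocation. Whether a patient wants another injection probably depends on how well the first one worked, and so on the arm. The PRP patients in the subgroup would then be the poorer responders to PRP, set against a broader cross-section of placebo patients. Some of those placebo patients may also have had PRP before the 12-month assessment.

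At stake is the reading of the result. A small or absent difference among re-injected patients could be reported as PRP not helping those who need repeat treatment, when selection and crossover could produce it without any such lack of effect. The primary comparison in all randomised patients and the sample size do not depend on this subgroup.

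**Working it through.** **Inputs from the protocol (Statistician report).** On significance and power: "The cut-off for statistical significance is set at 5% and desired power at 90%, with two-tailed tests applied". On spread: "the standard deviation for the change in score from baseline as no greater than 21". For the placebo change the authors "estimate a maximal change of 10", and for PRP they assume at least 27, so the difference is 17.

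**Reproducing the plan's own figure.** n per arm = 2 × (1.960 + 1.282)² × 21² / 17² = 2 × 10.51 × 441 / 289 = 32.07, rounded up to 33, or 66 in all. Then 66 / 0.65 = 101.5, giving 102 recruited, and 101.54 / 0.75 = 135.4 approached. All agree with the protocol, so its planning values are a fair basis for an illustration. The protocol gives no figure for the subgroup itself.

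**Assumptions not in the protocol.**
- A patient takes the second injection if the 6-month gain is below c = 10 (0 and 20 also tried).
- The 6- and 12-month changes are bivariate normal with SD 21 and means 10 and 27, with correlation ρ of 0.5, 0.7 or 0.9.
- The gain from a second injection is varied below.

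**Step 1: who enters.** The share entering is Φ((c − mean)/21).
- Placebo: Φ(0) = 0.50.
- PRP: Φ(−17/21) = Φ(−0.81) = 0.21.

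With 51 per arm before dropout, that is about 25 or 26 placebo and 11 PRP patients.

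**Step 2: selection alone.** Among those who enter, the mean 12-month change falls below its arm mean by ρ × 21 × φ(z)/Φ(z), where z = (c − mean)/21.
- Placebo: 21 × 0.399/0.500 = 16.76, times ρ.
- PRP: 21 × 0.2875/0.2091 = 28.87, times ρ.

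The gap is 12.12 × ρ. The subgroup difference is 17 − 12.12ρ when the 17-point effect lasts and the second injection does nothing:

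| ρ | Prognostic gap | Subgroup difference | All randomised |
|---|---|---|---|
| 0.5 | 6.1 | 10.9 | 17 |
| 0.7 | 8.5 | 8.5 | 17 |
| 0.9 | 10.9 | 6.1 | 17 |

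The sign is kept throughout. At ρ = 0.7, a threshold of 0 gives 32% v 10% entering and a difference of 7.7. A threshold of 20 gives 68% v 37% and 9.6.

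**Step 3: adding crossover.** Suppose every placebo member switches to PRP and gains 17, and PRP repeaters gain g. The subgroup difference is 17 − 12.12ρ − 17 + g = g − 12.12ρ. The all-randomised difference is 17 − 0.50 × 17 + 0.21 × g.

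| g | ρ = 0.5 | ρ = 0.7 | ρ = 0.9 | All randomised |
|---|---|---|---|---|
| 0 | −6.1 | −8.5 | −10.9 | 8.5 |
| 8.5 | +2.4 | 0.0 | −2.4 | 10.3 |
| 17 | +10.9 | +8.5 | +6.1 | 12.0 |

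If repeaters gain nothing, the share of placebo members who must switch before the sign turns is (17 − 12.12ρ)/17, or about 64%, 50% and 36% at the three correlations.

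**Step 4: waning instead of crossover.** With no second-injection effect and ρ = 0.7, a first-injection effect that has fallen to 8 or 5 points by 12 months gives a subgroup difference of about −0.5 or −3.5.

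**Step 5: no effect at all.** If PRP and placebo do not differ at 6 or 12 months, 50% of each arm enters and the subgroup difference is 0. In this model the distortion arises because the arm affects the 6-month response.

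**The case against.** Four points can be made for the plan.

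First, the phrase may mean treatments before the trial. It stands between two baseline factors, the Background describes escalating pre-trial options, and Table 1 requires failed conservative management. This reading is possible but less natural: previous treatment is already listed separately, every participant has had some, and the 6-month option is the only further trial treatment described. The ambiguity is real and belongs in the fix.

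Second, no PRP-versus-placebo test within the subgroup is spelled out; the text says only that the data will be investigated by these factors. That stands. A between-arm contrast is implied by the surrounding analyses, not stated, and describing re-injected patients within each arm would be legitimate.

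Third, no uptake rule is given, so response-driven uptake is an inference from the word required and from the pain rationale. That also stands, but under any uptake rule membership is settled after allocation and can differ by arm.

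Fourth, a reader might infer that the comparison must come out with the wrong sign, or that an apparent harm would reflect selection only. The protocol's figures do not support either. Selection with a lasting effect only attenuates. The negative values need most re-injected placebo patients at ρ = 0.7 to switch and gain the full 17 while PRP repeaters gain nothing, or the effect to wane. The protocol also offers a repeat of the original injection, so complete switching is an extreme case. Where crossover drives the result, the difference in all randomised patients falls as well, to 8.5 when repeaters gain nothing, so 17 is not the right comparator.

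**Conclusion.** The point holds in a limited form. On the natural reading, this subgroup is defined by a post-randomisation choice that the allocated treatment can influence, and its placebo members may since have had PRP. Any PRP-versus-placebo contrast within it lacks the protection of randomisation.

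Under the assumed re-injection rule, attenuation from selection alone is about 6 to 11 points of 17. With full crossover, the subgroup figure could lie anywhere from about −11 to +11, depending on the correlation and on what a repeat PRP injection adds, neither of which the protocol gives. Someone reading the result could not tell which case applied. The size is illustrative; the loss of randomisation does not depend on it. The matter should be corrected, but it concerns one exploratory analysis. How the 6-month option bears on the primary 12-month comparison is a separate question and is not settled here.

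**What to change.** State which treatments count as more than one.

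If the 6-month injection is meant:
- Make no between-arm inference in this subgroup.
- Report the number and type of second injections (repeat of the original, or PRP on request) by arm.
- Describe the outcomes of re-injected patients within each arm and label them non-randomised.
- Restrict comparative subgroups to variables fixed before randomisation.

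If pre-trial treatments are meant, say so and define the subgroup from baseline records.

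The change is a matter of wording. It alters no sample size, data collection or patient care, and does not question whether the option is offered. The cost is the loss of one exploratory comparison.
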